## Methods

The overall aim of the U-Age nursing home study is to evaluate effects and meanings of a person-centred and thriving-promoting intervention in nursing homes. More specifically, the following research questions will be explored:Will the intervention increase resident’s thriving (primary endpoint), and positively affect their experience of the care environment (secondary endpoint)?Will the intervention increase relatives’ satisfaction with care (primary endpoint), enhance their experience of visiting their relative and the nursing home, and positively affect their experience of the care environment (secondary endpoints)?Will the intervention increase staff’s job satisfaction (primary endpoint), decrease their stress of conscience, increase the perceived level of person-centredness of care and positively affect their experience of the care environment (secondary endpoints)?What are the experiences and meanings of the intervention as described by relatives and staff?

The study is designed as a multi-centre, non-equivalent controlled group before-after study with participating sites in Victoria (Australia), Oslo (Norway) and Västerbotten (Sweden). Two nursing homes at each site have been allocated to either intervention or control, in total three intervention and three control facilities across the three international sites. Study specific surveys will be used to collect data on primary and secondary endpoints, with study endpoints being analysed post-intervention, and at six-month follow-up. Qualitative research interviews will be conducted post-intervention to illuminate experiences and meanings of the intervention as described by relatives and staff.

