### Power calculation

Sample size calculations have been made based on a medium effect size of 0.30, a two-sided significance level of 0.05 and a power of 0.85. Calculations for the primary *resident* endpoint was based on unpublished results of TOPAS mean values of 154 and SD 22, indicating that a sample of 150 residents from each group would be sufficient to detect pre-post intervention differences of 6.2. Calculations of the primary *relative* endpoint was based on a previously reported Pyramid questionnaire mean of 76 and SD 21 for overall satisfaction in similar context [57], which indicates that a sample of 150 relatives from each group would be sufficient to detect significant pre-post intervention mean differences of at least 8.7. Calculations of the primary *staff* endpoint was based on a previously reported MJS mean of 81 and SD of 14 for job satisfaction in similar context [34], which indicates that a sample of 150 staff from each group would be sufficient to detect significant pre-post intervention mean differences of at least 3.4. Therefore, a total of at least 900 participants will be recruited.

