### Statistical analyses

Sample characteristics will be explored using descriptive statistics, and standard analyses adjustments will be made to adjust for baseline differences between groups should such exist. In cases of missing data, sensitivity analyses will be performed to compare results with complete case analyses [58], and different options for imputation will be considered and discussed with statisticians before making a final decision. Differences between intervention and controls will be tested with *χ*2 tests for categorical variables, and independent sample *t*-test for continuous variables. General linear mixed models will be used to test effects of the interventions on primary and secondary endpoints. Potential confounders will be included as covariates. *P*-values of *<*0.05 will be regarded as statistically significant and effect sizes of *>*0.3 will be regarded as clinically significant. IBM SPSS Statistics for Windows, version 22.0 (Armonk, NY, USA: IBM Corp. Released 2013) will be used to analyse data.

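### The detectable differences are stated as pre-post differences, but the design needs a between-arm contrast, for which the staff figure and probably the resident figure are too optimistic

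*Protocol article*

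**What the plan says.** The Methods section of the protocol article describes a "multi-centre, non-equivalent controlled group before-after study" with three intervention and three control homes. The section on inclusion criteria says homes are chosen purposively through the researchers' networks, and the article describes no randomisation.

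The Power calculation section opens: "Sample size calculations have been made based on a medium effect size of 0.30", with "a two-sided significance level of 0.05 and a power of 0.85". It then gives one figure per population:

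- Residents: based on "TOPAS mean values of 154 and SD 22", "a sample of 150 residents from each group would be sufficient to detect pre-post intervention differences of 6.2".
- Relatives: Pyramid mean 76 and SD 21; 150 per group; a pre-post difference of 8.7.
- Staff: based on "MJS mean of 81 and SD of 14 for job satisfaction in similar context", 150 per group "would be sufficient to detect significant pre-post intervention mean differences of at least 3.4".

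The section gives no pre-post correlation and no SD of change. The Data collection section says surveys go to both arms at baseline, post-intervention and six months and are anonymous. It does not say whether one person's responses can be linked across waves.

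The Statistical analyses section says "Differences between intervention and controls will be tested with" chi-square and independent-sample t-tests. Its next sentence gives general linear mixed models the task of testing intervention effects on the endpoints. Confounders enter as covariates, and the section promises adjustment for baseline differences if any appear.

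**The concern.** The arms were not formed at random, so they may start at different levels, and scores may drift over a 12-month programme. A pre-post change within one arm contains that drift. The control arm removes it only if change is compared between arms, or if post-intervention scores are compared with each person's baseline taken into account.

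A sample size stated for a pre-post difference is therefore stated for a quantity that does not answer the research questions. At the same pre-post correlation, the between-arm difference in change has a standard error √2 = 1.41 times that of a one-arm change. If the figures really are one-arm figures, the trial could miss the effects it says it can detect, and a null result would be read as stronger evidence than it is.

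**Working it through.** **Inputs.** From the Power calculation section: two-sided alpha 0.05, power 0.85, 150 per group, SDs 22 / 21 / 14 and detectable differences 6.2 / 8.7 / 3.4 (residents / relatives / staff throughout). Assumed: the pre-post correlation ρ, because none is given; 150 per arm at each wave; no clustering, because no intraclass correlation is given. Multiplier: 1.960 + 1.036 = 2.996.

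**Step 1: reproduce the stated figures**, using each stated SD directly.

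- One group, detectable = 2.996 × SD / √150: 5.38 / 5.14 / **3.43**.
- Two groups, detectable = 2.996 × SD × √(2/150): 7.61 / 7.27 / 4.84.

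The staff figure of 3.4 matches the one-group formula: n = (2.996 × 14 / 3.4)² = 152, and power at 150 is 84.5%. As a two-group comparison, 3.4 would need 305 per group and has 56% power at 150. The resident 6.2 and relative 8.7 match neither line.

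The effect size of 0.30 does not tie the three together. It corresponds to 0.30 × SD = 6.6 / 6.3 / 4.2, whereas the stated differences are 6.2/22 = 0.28, 8.7/21 = 0.41 and 3.4/14 = 0.24 SD. At 85% power, 0.30 needs 200 per group (two groups) or 100 (one group), not 150.

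**Step 2: between-arm difference in change.** SE = 2 × SD × √((1 − ρ)/150); detectable = 2.996 × SE; power = Φ(stated difference / SE − 1.96). ρ = 0 also covers unlinked waves.

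| ρ (assumed) | Detectable difference at 85% power | Power (%) at 6.2 / 8.7 / 3.4 |
|---|---|---|
| 0 or unlinked | 10.8 / 10.3 / 6.9 | 40.7 / 71.8 / 31.8 |
| 0.3 | 9.0 / 8.6 / 5.7 | 54.1 / 85.8 / 42.8 |
| 0.5 | 7.6 / 7.3 / 4.8 | 68.5 / 94.8 / 55.7 |
| 0.7 | 5.9 / 5.6 / 3.8 | 88.3 / 99.6 / 77.5 |
| 0.8 | 4.8 / 4.6 / 3.1 | 97.1 / >99.9 / 91.4 |

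Worked line, staff at ρ = 0.5: SE = 28 × √(0.5/150) = 1.617; 3.4/1.617 − 1.96 = 0.143; Φ = 0.557.

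**Step 3: correlation needed for the stated figures to hold as differences in change at 85% power.** ρ = 1 − (stated / detectable at ρ = 0)²:

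- Residents: 1 − (6.2/10.76)² = 0.67
- Relatives: 1 − (8.7/10.28)² = 0.28
- Staff: 1 − (3.4/6.85)² = 0.75

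**Step 4: linked baseline-adjusted comparison.** SE = SD × √(1 − ρ²) × √(2/150). At ρ = 0.5 this is 2.20 / 2.10 / 1.40. Power is 80% for residents (6.2/2.20 − 1.96 = 0.858), 98.5% for relatives and 68% for staff (3.4/1.40 − 1.96 = 0.469).

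**The case against.** The best defence is that pre-post, with a number given for each group, is shorthand for a difference in change. How the figures were derived cannot be established from the article, and only one of the three fits a one-group formula. That uncertainty stands. But the shorthand reading needs three different unstated correlations (0.67, 0.28 and 0.75), and the staff figure needs the highest.

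Several stronger readings are tempting, and the article does not support them.

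- A reader might infer that t-tests are the test of effect. The sentence after the one naming them assigns effects on the endpoints to mixed models. The t and chi-square tests, whose time point is not given, can be read as comparing sample characteristics. No within-arm test is listed, and baseline adjustment is promised.
- A reader might count the unnamed group-by-time term as an error. A condensed article may leave that detail to the analysis plan, and nothing in the text contradicts such a term.
- A reader might hold that the difference in change is the one admissible contrast. A linked baseline-adjusted comparison also uses the control arm. It is more precise here, though weaker protection when arms start unequal.
- A reader might conclude that all three endpoints are underpowered. Relatives are not at ρ of 0.3 or more, and at ρ = 0.8 all three exceed 85%.

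**Conclusion.** The point holds for the sizing. The detectable differences are worded for a pre-post change and are not tied to a contrast that uses the control arm. The staff figure, with the stated SD, is a one-group figure.

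For the between-arm contrast the shortfall is clear for staff: 32% power at 3.4 if waves are unlinked and 56% at ρ = 0.5, or 68% with a linked baseline-adjusted analysis at that correlation. It is likely for residents: 41% and 68.5% for the difference in change, or 80% baseline-adjusted. It is absent for relatives unless ρ is below about 0.3.

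These sizes rest on an assumed correlation, 150 per arm at each wave and no clustering within the six homes. The unlinked case is a live possibility: the surveys are anonymous, people join throughout, and the Discussion acknowledges high turnover of residents and staff. The article gives no basis for relying on the high correlations that would rescue the staff figure.

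**What to change.** In the Power calculation section, restate the detectable differences, or the power at 6.2 / 8.7 / 3.4, for the between-arm contrast. State the correlation or SD of change used, and give the unlinked case alongside. Show how 150 per group follows, or say that the number is fixed by the size of the homes if that is so.

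In the same edit to the Statistical analyses section, say that this contrast is the mixed-model test of effect for each primary endpoint: the group-by-time coefficient from baseline to post-intervention, or the baseline-adjusted equivalent if responses are linked.

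The cost is wording and a recalculation. Both arms are already surveyed at every wave. If the sponsor instead wanted 85% power for staff at 3.4, the difference in change would need 305 per arm at ρ = 0.5 or 609 if unlinked. Restating the detectable difference is the practical course.

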### Statistical analyses

Sample characteristics will be explored using descriptive statistics, and standard analyses adjustments will be made to adjust for baseline differences between groups should such exist. In cases of missing data, sensitivity analyses will be performed to compare results with complete case analyses [58], and different options for imputation will be considered and discussed with statisticians before making a final decision. Differences between intervention and controls will be tested with *χ*2 tests for categorical variables, and independent sample *t*-test for continuous variables. General linear mixed models will be used to test effects of the interventions on primary and secondary endpoints. Potential confounders will be included as covariates. *P*-values of *<*0.05 will be regarded as statistically significant and effect sizes of *>*0.3 will be regarded as clinically significant. IBM SPSS Statistics for Windows, version 22.0 (Armonk, NY, USA: IBM Corp. Released 2013) will be used to analyse data.

### Research interviews

Group and individual interviews will be conducted to generate narrative research data for analyses of relatives’ and staff’s experiences of the intervention. Group interviews will consist of four to six participants in each group, and aims to stimulate broad discussion and sharing of experiences across units, which then can be followed up in individual research interviews. All interviews will be conducted with a purposefully selected sample of staff and relatives from the three intervention sites. Participants will be selected based on their willingness and ability to provide rich data. A total of 25 participants from each international site (*N* = 75) will be recruited for participation in group and individual interviews. Field notes, audio-recordings and verbatim transcriptions will be employed to document data and enable analyses and interpretations.

All interview data will be subjected to a phenomenological hermeneutical analysis to interpret for meanings of the lived experiences of the intervention. The analytical approach will follow the steps outlined by Lindseth & Norberg [59], involving a dialectical movement between naïve interpretation, structural analyses and the evolving comprehensive understanding [59].

### Study protocol amendments

All study sites will follow the study protocol. If modifications to the study protocol will be necessary, they will be discussed and agreed upon in consensus between the research group and the local facilities before implementation to protect the integrity of the intervention. All changes will be documented in a memorandum.

### Dissemination policy

The results of the study will be reported in international peer-reviewed journals as well as at national and international conferences, and for relevant society and community stakeholders as appropriate.

## Discussion

This protocol outlines the design and procedure for an international multi-site trial within nursing homes. Factors such as limited research cultures, high turnover of staff and residents, and unpredictable external forces such as regulatory organisational changes, suggest that conducting complex interventions in nursing homes is challenging [60]. Therefore, this study protocol can be regarded an important blueprint for both the conduct and evaluation of the intervention, as well as for the communication of information to stakeholders and/or the scientific community. A number of elements and processes are described based on experiences from interventions carried out in similar contexts, such as the theoretical and pedagogical framework for the intervention [61–64]. Anchoring the intervention in a theoretical framework consisting of established theories and evidence-based interventions, as well as a pedagogical framework that moves between knowledge translation, generation and dissemination is a strength of the study. Additionally, previous experiences from similar implementation protocols [35, 63] can be seen as strengthening the study.

The multisite approach can be a strength as well as a weakness of the study, a strength in the sense that the processes, experiences and results will have international applicability and relevance, and a weakness in the sense that there are dimensions that risks deviating slightly between sites. Thus, balancing contextual relevance with standardised content will be a challenge. To secure that the intervention will be as identical as possible across the three sites, the same detailed education material and facilitators guide will be used across sites, and weekly calibration meetings will be held between the three researchers leading the intervention at each site. The collaboration between the research group and the nursing home management and direct care seems essential for a successful intervention. Therefore, the choice of including nursing homes from the researchers’ existing network is regarded as a strength of the study. However, this also excludes the possibility of other nursing homes in need for improvement to participate. Thus sample representativity can be seen as a weakness of the study.

In terms of the study population, frail older people have often been excluded from research due to their vulnerable position and impaired possibility to provide informed consent. However, as the proportion of frail older people increases, the importance of developing research-based knowledge about good care increases, as well as the need to include residents’ perspectives. A main goal of introducing person-centred care in nursing homes is to shift focus from tasks to the person. This study can be seen to challenge those existing models for nursing home care that focuses mainly on the completion of tasks and/or medical care. This study will instead promote a model that focuses on supporting thriving, satisfaction and general wellbeing in residents as well as in relatives and staff. The study can contribute to the knowledge on how to operationalise and implement person-centred care in nursing home contexts. The results are expected to provide evidence to inform further research, policy and practice development on if and how person-centred and thriving promoting care can improve wellbeing and satisfaction for residents, relatives and staff within nursing homes.

## Abbreviations

DCM: Dementia Care Mapping
MJS: The Measure of Job Satisfaction
P-CAT: Person-centred Care Assessment Tool
PCN: The Person-Centred Nursing framework
TOPAS: The Thriving of Older People Assessment Scale
